### Sample Size Considerations

A total of 1050 individuals will be targeted for recruitment. Assuming a 5% loss to follow-up, this corresponds to 1000 evaluable individuals at the end of the study. The study has been designed to predict postprandial glucose responses based on individual characteristics and 1000 participants followed for 14-days will result more than 4 million glucose readings (assuming glucose readings from the CGMs every 5 minutes) and 42,000 meals (assuming 3 meals per participant per day). This volume of data will also provide more than 80% power to detect correlations of a magnitude of *r*=0.13 (*R*^2^=0.02) with *P*<.005. We will also be sufficiently powered to detect effects of *r*=0.17 (*R*^2^=0.03, ie, explaining 2.7% of interindividual variation) with *P*<.001, that is, accounting for 5000 independent hypothesis tests.

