### Statistical Analysis Plan

The study’s primary outcome is PPGR. Following the Wolever and Jenkins method [31], as adapted by Zeevi et al [18], Mendes-Soares et al [20], and Berry et al [32], logged meal times and continuous glucose measurements will be used to calculate the incremental area under the curve. Before conducting analyses, meals logged less than 30 minutes apart will be merged and meals logged within 90 minutes of other meals will be removed. Meals that are very small (<15 g and <70 calories), very large (>1 kg), with implausibly low PPGR values (ie, a PPGR < 5 mg/dL·h after consuming ≥ 40 g of carbohydrates), that are incompletely logged, and which are consumed in the first and last 12 hours of the CGM connection will also be removed. To reduce noise, the median of all glucose values from the 30-minute period before the meal will be taken as the initial glucose level, above which the incremental area will be calculated. Meals that had incomplete glucose measurements in the time window of 30 minutes before and 2 hours after the logged mealtime will be filtered out.

Descriptive statistics will be used to plot the range of PPGRs responses to standardized test meals as well as the correlation between PPGR and the nutritional composition of the logged meals (ie, carbohydrates, fat, and protein).

A machine learning predictor will be developed based on stochastic gradient boosting regression (XGBoost, version 2.2.1; The XG Boost Contributors) [33] using the XGBRegressor class. PPGR will be predicted as the sum of predictions from thousands of decision trees. Trees will be inferred sequentially, with each trained on the residual of all previous trees. The features incorporated in each tree are selected by an inference procedure from features representing meal content (ie, calorie, protein, carbohydrate, and fiber content), meal timing, baseline demographics (ie, age, sex, predominant diet, health conditions, family history, and current medications), baseline survey results (ie, WHO STEPS, WHO-5, Diabetes Distress School, Wilson Adherence Scale, and Pittsburgh Sleep Quality), baseline biometric values (ie, blood pressure, heart rate, weight, height, and body measurements at the upper arm, thigh, calf, waist, and hips), baseline laboratory values (complete blood count, HbA_1c_, blood electrolytes, creatinine, cholesterol, and urinalysis), as well as CGM, heart rate, and activity data.

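### The threshold P<.001 does not account for 5000 independent tests; at family-wise 0.05 that needs P<.00001, and the printed effect size fits the stricter value

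*Protocol article*

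**What the plan says.** All of this is in the protocol article, Methods, Sample Size Considerations.

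- Recruitment and evaluable number: the target is 1050, with a 5% allowance for dropout. The article says that "this corresponds to 1000 evaluable individuals at the end of the study".
- Power statement for the smaller effect, r=0.13: "more than 80% power to detect correlations of a magnitude of *r*=0.13 (*R*^2^=0.02) with *P*<.005".
- Power statement for the larger effect, r=0.17: power is called adequate, and the effect is also given as an R-squared of 0.03 and as "explaining 2.7% of interindividual variation". The threshold attached to this statement reads "with *P*<.001, that is, accounting for 5000 independent hypothesis tests".

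The second statement gives no numerical power. Neither statement gives a family-wise level, a correction method or the sidedness of the tests. The section introduces both by pointing to the volume of glucose readings and meals.

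**The concern.** The sentence does not leave multiplicity to another document. It names a threshold and says what that threshold achieves, and the two do not match: a per-test level of .001 is far too loose for 5000 tests under any usual family-wise target.

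One of the study's aims, in the Objective of the abstract, is to identify factors associated with differences in PPGR, and the Statistical Analysis Plan section lists a long set of candidate features. This is the only place where the article ties a P value to a number of tests. Anyone who later used .001 in the belief that it controlled error across 5000 tests would have almost no family-wise control.

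**Working it through.** **Inputs.** From Sample Size Considerations: 1000 evaluable participants; r=0.13 at P<.005 with more than 80% power; r=0.17 (R-squared 0.03, 2.7%) at P<.001; 5000 independent tests. Assumed, because the article does not say: family-wise level 0.05, two-sided tests, and 80% power for the r=0.17 statement, carried over from the r=0.13 statement.

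**1. The plan's own figures.** 1050 × 0.95 = 997.5, in effect 1000. Power for a correlation by Fisher's z is Φ(atanh(r)·√(n−3) − z), where z is the normal quantile at 1−α/2. With n=1000, √997 = 31.575. For r=0.13 at .005: 0.13074 × 31.575 = 4.128; 4.128 − 2.807 = 1.321; power 90.7%. The printed statement of more than 80% power for r=0.13 is therefore true. The statement that .001 accounts for 5000 tests cannot be reproduced.

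**2. Threshold for 5000 tests.**
- Bonferroni: 0.05/5000 = 0.00001. Šidák: 1 − 0.95^(1/5000) = 0.0000103.
- Tests covered by .001 at family-wise 0.05: 0.05/0.001 = 50.
- Ratio of printed to required threshold: 0.001/0.00001 = 100.
- Expected false positives among 5000 true nulls at .001: 5000 × 0.001 = 5.
- Family-wise error at .001 with 5000 independent true nulls: 1 − 0.999^5000 = 99.3%.

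**3. Power for r=0.17 at each threshold.** atanh(0.17)·√997 = 0.17167 × 31.575 = 5.420.
- At .001: 5.420 − 3.291 = 2.130; power 98.3%.
- At .00001: 5.420 − 4.417 = 1.003; power 84.2% (87.6% one-sided).

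A simulation of the t-test for a correlation (400,000 draws) gave 98.3% and 84.2%. At .00001, 80% power for r=0.17 needs 942 participants; with 950, power is 80.7%.

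**4. Which threshold fits the printed effects.** The correlation detectable with 80% power is tanh((z + 0.842)/√997).

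| Two-sided α | Detectable r, n=1000 | R-squared |
|---|---|---|
| .005 | 0.115 | 1.3% |
| .001 | 0.130 | 1.7% |
| .00001 | 0.165 | 2.72% |

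The last row rounds to all three printed figures for the second effect: r=0.17, R-squared 0.03 and 2.7%. The printed r=0.13 falls on the .001 row, not on its own .005. At .001 its power is 0.7989, or 80% rounded, against 90.7% at .005.

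**5. Unit of analysis.** Every match above comes from 1000 independent participants. Treating 42,000 meals as independent would make power essentially 100% for either effect, so the volume of data is not what produces these figures.

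**The case against.** The strongest reply is that this is a printing slip with no effect on the design. The effect sizes indicate that the calculation used 0.00001, the power claim survives at that level, and no analysis described in the article uses .001 as a decision rule. The Statistical Analysis Plan section describes descriptive plots and correlations, a gradient-boosting predictor, a Pearson correlation with bootstrapped standard error, and an area under the ROC curve. Most of this stands. The 99.3% and the 5 false positives describe what .001 would do if applied to 5000 true nulls; they are not a forecast for this study. What does not fall away is that the sentence, as printed, is wrong about the error control it claims.

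Three stronger readings are tempting, and the documents do not support them.

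- **That the power calculation used an error rate 100 times too lenient.** The printed effect fits 0.00001, so the evidence points to the printed threshold.
- **That 2.7% is an arithmetic error because 0.17 squared is 2.9%.** An unrounded r of 0.165 gives 2.72% and prints as 0.17, so this is rounding.
- **That the meal count is unattainable.** The article gives "42,000 meals (assuming 3 meals per participant per day") as a labelled gross assumption. Table 1 has a fasting entry for the first breakfast, and meals "which are consumed in the first and last 12 hours of the CGM connection will also be removed". The latter is an analysis filter, though, and does not contradict an expected volume. Participants also log snacks and may repeat test meals, so scheduled meals set no upper limit on logged ones.

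**Conclusion.** The stated threshold is wrong. At family-wise 0.05, P<.001 accounts for 50 independent tests, not 5000, and is 100 times larger than the 5000-test claim requires. The family-wise level is an assumption, but the finding does not hinge on it: 5000 independent true nulls at .001 carry a 99.3% chance of at least one false positive, which no one would accept as control.

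The sample size and the power conclusion stand. With 1000 independent participants and two-sided testing, power for r=0.17 is 84.2% at .00001. That the calculation used .00001 is an inference from the agreement of the effect sizes, because the article does not show its working. The r=0.13 line points the same way: its claim is true as printed, but its effect size matches .001 rather than .005, so that threshold may also be misprinted.

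**What to change.** 1. For the 5000-test claim, replace P<.001 with P<.00001 and give the power: 84% for r=0.17, or 80% for r=0.165 (R-squared 2.7%). If .001 is what was meant, say that it covers 50 tests; power for r=0.17 is then 98.3%.
2. State the family-wise level (0.05 is assumed here) and that the tests are two-sided, if they are.
3. Use the corrected threshold wherever control over 5000 tests is claimed for factors associated with PPGR.
4. Say that these power figures rest on 1000 independent participants, not on the number of readings or meals.
5. Check the r=0.13 line against the source calculation. Power is 90.7% at .005 and 80% at .001, so either the threshold or the description of the power may need changing.

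The cost is a few words in one paragraph. Recruitment, data collection and the planned modelling do not change. The one visible difference is that power for r=0.17, if quoted, is 84% at the corrected threshold rather than the 98% implied by .001.

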## Results

Data collection commenced in May 2022, and the results will be ready for publication by October 2025. Results from our study will generate data to facilitate the creation of machine learning models to predict individual PPGR responses and to facilitate the prescription of personalized diets for individuals with T2D.

## Discussion

### Study Implications

This study will provide the first large scale examination of variability in blood glucose responses to food in India and will be among the first to estimate PPGR variability for individuals with T2D in any jurisdiction. We hypothesize that there will be substantial interindividual variability in PPGR and that, based on the data collected from this study, machine learning models will be able to accurately predict individual PPGR responses. This will facilitate the prescription of truly personalized diets for individuals with T2D.

These results will be particularly important in the context of the rapidly rising prevalence of T2D in India [34]. Along with medications and physical activity, diet is a key tenant of effective blood glucose control [15]. Like in other jurisdictions, guidelines call for individualization of meal planning, which is sometimes referred to as “Medical Nutritional Therapy.” Despite this, personalization of dietary plans are generally based upon broad constructs like age, activity level, health status, and preferences, and, for all patients, tend to emphasize overall calorie reductions and minimization of carbohydrate [16]. especially added sugars and refined grains, in favor of the consumption of nonstarchy vegetables and foods that are high in protein [35].

However, emerging data demonstrates that there are marked interindividual responses to food [17], attributed to differences in physical activity [36], gut microbiome [18,19,37], and genetics [38], including in variations in skeletal glucose transporters related to insulin resistance [39]. For example, a study conducted in the United States among nondiabetic individuals with a mean BMI of 27 found PPGR to a standardized meal of bagel and cream cheese ranged from 6 to 94 mg/dL·h [20]. A similar study conducted in Israel enrolled nondiabetic individuals of whom 3-quarters had a BMI ≥ 25 and found mean PPGR to bread and butter of 44 mg/dL·h but the bottom decile had responses of ≤ 15 mg/dL·h and the top decile has responses ≥ 79 mg/dL·h [18]. Similar data have been generated for individual without diabetes in the United Kingdom and the United States [19,20], and for individuals with type 1 diabetes in Israel [40].

There is exceptionally limited data for variability in PPGR for individuals with T2D in the peer-reviewed although it is highly likely that such variability exists [22]. The primary goal of our study is to fill this void and to generate an India-specific machine-learning models on the basis of which PPGR can be predicted with high accuracy for T2D. Similar models have been built in other jurisdictions. For example, a machine learning algorithm trained on CGM data, dietary, activity, anthropometrics, and gut microbiota for nondiabetic individuals in Israel was much more accurate at predicting PPGR than generic models based on the carbohydrate content or the amount of calories in a meal [18]. A separate US-based study had similar findings [20].

Among individuals with diabetes, a study in the Netherlands that included a small number of individuals with T2D along with individuals with prediabetes and normal glucose metabolism, a machine learning model based on CGM data was highly accurate in predicting future glucose values but this study did not specifically evaluate the ability to predict PPGR [41]. A US study of 1000 patients of whom 1-quarter had T2D found that a machine learning model trained on CGM, HRM data and food logs was highly accurate at predicting PPGR but this study has, to our knowledge, only been published in abstract form [22]. These studies have all relied on CGM data to make their predictions. While these devices are increasingly used, practice guidelines do not recommend their long-term use for most individuals with T2D [42]. Accordingly, a key goal of our study will be to explore the ability to predict PPGR response without reliance on CGM data or with very limited blood glucose data from patients.

### Limitations

There are several limitations to our approach. Our approach is purposely pragmatic and is intended to simulate real-world circumstances for individuals with T2D living in India. Similar to studies conducted in other jurisdictions, we rely on self-reported dietary and activity information. And, while we are auditing patient logs on an ongoing basis, there may nevertheless be issues with protocol adherence that may undermine the accuracy of the data we collect. Participants are being recruited from clinics, predominantly caring for individuals with diabetes, are required to have functional English literacy and a cellphone capable of running study specific devices. Thus, our results may not be fully generalizable to patients who do not fulfill these criteria. Finally, some of the enrollment has overlapped with the COVID-19 pandemic, which may have influenced access to health care, dietary practices, and glucose control for individuals with T2D.

### Conclusion

In conclusion, this study will provide the first large scale examination variability in blood glucose responses to food in India and will be among the first to estimate PPGR variability for individuals with T2D in any jurisdiction. Results from our study will generate data to facilitate the creation of machine learning models to predict individual PPGR responses and to ultimately facilitate the prescription of truly personalized diets for individuals with T2D.

## Abbreviations

CGM: continuous glucose monitor
HbA_1c_: hemoglobin A1c
PPGR: postprandial glucose response
ROC: receiver operating characteristic
STEPS: STEPwise Approach to Non-Communicable Disease Risk Factor Surveillance
T2D: type 2 diabetes mellitus
WHO-5: World Health Organization-Five Well-Being Index
